### Blinding

This is a single-blind cluster randomised trial. Resident and staff participants within each participating unit are recruited, and baseline data collected, prior to the random allocation of units to control and intervention groups. Because of the nature of the intervention, it is not possible to blind participants (residents with dementia or staff working in the units) to group allocation. Outcome assessment is protected by blinding the research nurses involved in data generation and collection to the group allocation of participating units, staff and residents. Data analysis is undertaken by researchers and statisticians blinded to group allocation by providing a database of outcomes identifiable only by number.

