## Methods/Design

The DARES study is a two-group, single-blind cluster randomised trial conducted in public and private long-stay residential settings in Ireland (see Figure 1). Randomisation to control and intervention is at the level of the long-stay residential unit. Care staff within the long-stay residential units allocated to the intervention group receive the structured education reminiscence-based programme. Trained staff use reminiscence with eligible consenting residents within the intervention long-stay settings. Residents in long-stay settings allocated to the control group receive usual care. Blinded outcome assessment is undertaken at baseline and at 18-22 weeks post randomisation. A comparison of outcomes between the intervention and control sites is made to examine if differences exist, and to what extent, between control and experimental groups. Ethical approval has been granted by the Research Ethics Committee of the National University of Ireland, Galway and from each of the appropriate county/hospital-based ethics committees responsible for the public long-stay units in the trial.

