## Outcomes

Outcomes are measured for both the control and experimental group at baseline (T_1_) (following consent and prior to randomisation and cluster allocation) and again at 18-22 weeks post randomisation (T_2_).

Each participating long-stay unit is assigned a RN who is responsible for blinded outcome assessment for all participating residents within that unit. All research nurses undertake a two-day preparation programme consisting of:

i) Training on the procedures and protocols surrounding the recruitment of participants and delivery, assessment and recording of all outcome measurements

ii) Simulated completion of all data collection instruments and forms

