### Primary Outcome

The primary outcome is quality of life of residents as measured by the Quality of Life-AD (QOL-AD) instrument [26]. The QOL-AD covers 13 domains of quality of life. It is designed to provide both a care recipients (CR) report and a caregiver's (CG) report of the resident's QOL. The measure has good internal consistency, validity and reliability and has been recommended by the European consenus group on outcome measures for use in the measurement of psychosocial interventions in dementia [34].

The QOL-AD is administered as a structured interview using standardised instructions. The RN administers the QOL-AD form to the CR, regardless of the severity of dementia. A staff member who is familiar with the CR completes the caregiver proxy version of the QOL-AD. The RN is available to advise the designated staff member on how to complete the proxy version of the QOL-AD form, answering any questions that may arise in the process.

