### Secondary Outcomes

(a) The level of agitation in resident participants is measured using the Cohen-Mansfield Agitation Inventory (CMAI). The CMAI is a 29-item scale specifically developed to assess the frequency of agitated and disruptive behaviours [35]. The questionnaire has four domains: physical/aggressive, physical/non-aggressive, verbal/aggressive, verbal/non-aggressive. The measure has good validity and reliability [36,37]. The CMAI is administered by the RN, following consultation with relevant staff who are aware of the resident's behaviour over the previous two weeks.

(b) Depression in resident participants is assessed using the Cornell Scale for Depression in Dementia (CSDD) [38]. The scale was specifically developed to assess signs and symptoms of major depression in people with dementia across five broad categories. As some people with dementia may not be able to provide reliable reports, the CSDD uses a comprehensive interviewing approach, through two semi-structured interviews: an interview with a main carer and an interview with the person with dementia. Good validity and reliability have been demonstrated for the scale [38].

(c) Staff care burden is assessed using a modified version of the Zarit Burden Interview [39]. The scale was initially developed to assess carer burden on the relatives of impaired older people. The original questionnaire contains 22 questions rated on a 4-point Likert scale and was designed to assess the impact of caring on the physical and emotional well-being of carers. The original scale has satisfactory reliability and validity [40]. A modified version of the original scale is used in this study, containing 13 questions selected for their appropriateness and applicability to nursing care staff in residential long-stay units. The modified scale has performed satisfactorily when used to assess burden on nursing staff caring for people with dementia in a Canadian long-stay setting [41].

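### Outcome assessment is called blinded without exception, but the caregiver QOL-AD and all three listed secondary outcomes rest wholly or partly on unblinded staff at T2

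*Protocol article*

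**What the plan says.** The blinding claim appears in several places in the protocol article, each time without an exception.

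- Methods/Design: "Blinded outcome assessment is undertaken at baseline and at 18-22 weeks post randomisation". The Abstract says the same.
- Outcomes: each unit has one research nurse, who is "responsible for blinded outcome assessment for all participating residents within that unit".
- Blinding: "Outcome assessment is protected by blinding the research nurses involved in data generation and collection to the group allocation". Those who analyse the data are blinded too.

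The Blinding section also says that "it is not possible to blind participants (residents with dementia or staff working in the units) to group allocation", and that participants are recruited and "baseline data collected, prior to the random allocation of units to control and intervention groups".

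The Primary Outcome and Secondary Outcomes sections then say where the data come from. For the caregiver QOL-AD, a staff member who knows the resident "completes the caregiver proxy version of the QOL-AD", with the nurse on hand to advise. For agitation, "The CMAI is administered by the RN, following consultation with relevant staff". For depression, the CSDD uses "an interview with a main carer and an interview with the person with dementia". Staff burden is measured with a modified Zarit interview. The care-recipient QOL-AD is an interview of the resident by the nurse, and the sample size text uses this version.

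**The concern.** Blinding the person who records a rating does not blind the rating when its content comes from someone who knows the allocation. In intervention units each participating resident is linked to a nurse and a care assistant who have taken the programme and who deliver reminiscence to that resident. They are obvious candidates for the familiar staff member or the main carer, and the outcome descriptions do not rule them out. Their curriculum covers understanding the person with dementia and challenging behaviour, so training could change how they perceive and report a resident, apart from any change in the resident. Control informants have no such training.

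At stake is what the trial can conclude on agitation, depression, staff burden and caregiver-reported quality of life. A difference in reporting would look like a treatment effect, and the published report would describe it as coming from blinded assessment.

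**Working it through.** No figure in the plan decides this point. The check traces each measure to its source and then asks whether the planned analysis could remove an allocation-dependent reporting difference.

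**Step 1: source of each measure at T2** (Primary Outcome and Secondary Outcomes sections)

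| Measure | Who collects or records | Who supplies the content | Unblinded staff input |
|---|---|---|---|
| Care-recipient QOL-AD | Blinded nurse | Resident | None |
| Caregiver QOL-AD | Staff member, nurse advising | Staff member | Whole |
| CMAI | Blinded nurse | Nurse, after consulting staff | Part |
| CSDD | Not stated by name | Main carer and resident, one interview each | Part, if the carer is staff |
| Modified Zarit | Not stated by name | Staff, on their own burden | Whole |

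Staff supply all of two measures and part of two more: 2 + 2 = 4 of 5. That is all three listed secondary outcomes and one of the two QOL-AD versions.

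**Step 2: which visits are exposed.** Baseline is taken before allocation, so T1 ratings cannot reflect knowledge of it. The exposure is confined to T2.

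**Step 3: whether baseline adjustment helps.** Let θ be the true effect on a staff-informed measure. Let b₁ and b₀ be the average shifts in T2 reporting caused by knowing the allocation (and, in the intervention arm, by having been trained). Neither shift is present at T1. Then:

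- expected adjusted difference = θ + (b₁ − b₀)

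Analysis of covariance on the T1 score removes chance differences at baseline and stable habits of a rater. It leaves (b₁ − b₀) untouched, because that term arises after T1. Multi-level modelling corrects the standard error for clustering, not this term, and more residents would not shrink it.

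**Step 4: reach to the care-recipient QOL-AD.** Staff do not rate this version, so Step 3 does not apply to it through staff. The remaining route is the nurse. One nurse assesses all participating residents of a unit and also consults the unblinded staff for the CMAI. With 17 residents per unit, one disclosure made before the resident interviews could affect up to 17 of them.

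**Step 5: size.** The document gives no value for b₁ or b₀ and no sign for their difference. The 4-point target was set for the care-recipient version, so it is not a yardstick for a shift in the caregiver version. No size is given here.

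**The case against.** The strongest reply is that the article already discloses this. It calls the trial single-blind, says plainly that staff cannot be blinded, claims blinding only for nurses and analysts in the Blinding section, and names the source of the resident measures. This stands in part: nothing is concealed, and the fault lies in the unqualified label elsewhere. It does not dispose of the point, because the admission is never carried through to the outcomes it affects.

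A second reply is that informant rules, interview order and logging of unblinding belong in the nurses' assessment procedures, which the article mentions but does not reproduce. That is fair. The absence of such rules is therefore not itself the fault. The fault is a statement that the article's own outcome descriptions do not support.

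Some stronger readings are tempting but unsupported:

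- **That the main result is staff-rated.** The version used for sizing comes from the resident. Residents are not blinded either, but that is a separate limitation which the article admits.
- **That trained dyad members do act as informants.** The text only fails to exclude it.
- **That the carer accounts for half of the CSDD.** The article gives two interviews and no weighting.
- **That informants from outside the dyad should be required.** They would still be unblinded and might know the resident less well. Where T1 ratings already exist, a new informant at T2 would also mix a change of rater into the change in score.

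**Conclusion.** The point holds as a mismatch between the blinding claimed and the way four of five measures are obtained. At T2 the caregiver QOL-AD and staff burden come from unblinded staff. The CMAI and CSDD do so in part; for the CSDD this assumes that the main carer is a staff member, which is the natural reading in a long-stay unit but is not stated. The bias is possible rather than shown, its size and direction cannot be derived, and baseline adjustment would not remove it.

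A reader might infer that the trial's conclusion on quality of life is undermined. The document does not support that: the care-recipient QOL-AD is collected by a blinded nurse, and its exposure through staff is limited to possible unblinding of that nurse.

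**What to change.** 1. Restate the blinding by outcome wherever it is claimed. Research nurses and analysts are blinded; the caregiver QOL-AD, CMAI, CSDD carer interview and staff burden rest on unblinded informants and will be interpreted as such. For staff burden this wording is the only remedy available.
2. At T2, have the nurse complete the care-recipient QOL-AD interviews in a unit before consulting its staff, and record whether and when allocation was revealed.
3. Keep the same informant for a resident at T1 and T2 where possible, and record whether that person belongs to the resident's dyad, so that results can be described by informant type.

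If the full procedures already contain items 2 and 3, only item 1 is needed. The cost is wording, an instruction to the nurses, some scheduling within each visit and two extra recorded items. No additional staff are needed. The blinding will read less favourably, but accurately.

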### Intervention

The structured education programme for staff was developed using input from a number of different sources:

• A review of the relevant literature on reminiscence, psychosocial interventions and care for people with dementia

• A concept analysis of reminiscence, undertaken to identify the key attributes of reminiscence

• Interviews with experts from the fields of dementia, dementia education, psychiatry of old age, occupational therapy within psychiatry of old age, psychology and reminiscence

• Interviews with care staff in public and private long-stay units to establish their training needs and preferences for training modalities

• Interviews with people with dementia and with relatives of people with dementia to establish what they feel is important in the care of people with dementia

• A review of standards, guidelines and examples of international best practice on dementia care and dementia education

The education programme is founded on the DARES programme philosophy of empowerment of staff participants, including identifying what participants perceive to be important and what they feel they need to know. The concepts of learner-centeredness and adult learning are at the core of the programme, and those teaching the programme adopt a facilitator-participant role, as this is considered central to realising the empowerment philosophy. Staff participants are trained to enable them to incorporate reminiscence strategies when developing person-centred care plans.

The curriculum incorporates the following sessions:

• Introduction

• Understanding the person with dementia

• How memory works

• Reminiscence explained

• Communicating with persons with dementia

• Behaviours that challenge

• Using reminiscence in practice

• Person-centred care planning for people with dementia

The structured education programme is facilitated by experienced educators and delivered over three days: two consecutive days at the beginning of the intervention and a third day six weeks later. The DARES research team provide telephone support to staff participants during the study period, as well as conducting one support visit to each unit.

Each resident participant in the long-stay unit in the intervention group is linked with a nurse and care assistant who have attended the education programme. Each staff dyad is responsible for using reminiscence with three to four resident participants and for embedding reminiscence within the resident's care plan. Each staff dyad engages the resident with dementia in reminiscence on at least four occasions per week (i.e. one planned formal session and three spontaneous sessions). Staff in the intervention record formal and informal reminiscence conducted with each resident. Staff also complete a life history in order to provide a foundation for the reminiscence sessions.

### Control Group (Usual Care)

Residents in the control group receive usual care where a resident's care is guided by current nursing and medical care plans. This can vary between and within units, but in principle at least, the various elements of care on offer to this group are also available to those in the intervention group. Therefore, the trial examines the additional effects of reminiscence arising from the structured education programme. While the complexity and potential heterogeneity of usual care is acknowledged, every effort is made to describe clearly the components of usual care for residents with dementia through interviews with managers or staff nurses, and through documentary analysis of the residents care plan.

### Consent

The Director of Nursing/Nurse in Charge or their nominee identifies all residents fulfilling the trial inclusion criteria, including the residents' likely ability to participate and the potential benefits or stresses for him/her arising from participation. Residents who would be unduly distressed by inclusion in the study are not asked to consider participation.

Care staff introduce the research nurse (RN) to each potential participant. The RN spends time building a rapport with each potential participant, explains the study in simple language, and explores whether the resident is interested in being included in the trial. If the resident indicates that he/she is not interested in participating in the study, the RN will not pursue consent any further. For residents interested in participating, the RN provides written information about the study. Information about the study is also provided to the relevant next of kin of potential participants. The various information sheets inform potential participants and their families of the purpose, process, potential benefits and harms of the trial, data collection procedures, time commitment, voluntary participation, the right to withdraw (without prejudice to care), as well as providing an assurance of confidentiality.

In seeking consent, it is made clear that participation is voluntary and that the resident has the right to withdraw at any point without prejudice. The resident is given opportunities to indicate how they feel about being involved, to ask questions, clarify issues or to withdraw if they so desire. Where a potential participant is willing to engage in the trial and expresses an understanding of the purpose of the study and its voluntary nature, as well as expressing a choice to participate, the RN will finalise the consent process directly with the resident.

In instances where it is not possible to gain consent directly, consent by proxy is used, where the older person's next of kin is asked to give formal written consent on behalf of their relative. The next of kin is asked to make their decision on the basis of their knowledge of the individual's prior attitudes and values [32]. All next of kin are provided with information on the study, including material on benefits and risks. There is growing evidence that there are differences between the views of people with dementia and their proxies [33] so where possible the perspective of the older person with dementia is sought in the first instance.

Assent is assessed throughout the study for all residents irrespective of whether consent has been obtained directly or by proxy. Where assent is not forthcoming at any stage, the resident is withdrawn from the study without consequence.

## Adverse Events

Reminiscence is this study is used to assist the resident in recalling positive and happy thoughts that enhance communication and connectivity with self and others, thereby improving their quality of life. The risks and harmful side-effects from participating in DARES are, therefore, likely to be low and no adverse reactions were reported from the two pilot sites or from previous trials in the literature [16]. During the structured education programme, staff are trained to deliver reminiscence training that fosters positive thoughts and happy memories. Staff also learn how to respond to situations where reminiscence results in the recall of negative or upsetting events in the lives of residents. Staff must record any such events on the Reminiscence Record Sheets. The research team ask staff during each point of contact (support visit, support telephone calls) whether any adverse events have occurred and offer support as required. If a resident becomes unduly distressed because of reminiscence, staff will respond to the situation in an appropriate manner and if unresolved will raise the issue with the research team. Prospective participants and their families are fully informed of the potential risks and benefits of the project. The resident has the right to opt out of the study at any stage.

## Outcomes

Outcomes are measured for both the control and experimental group at baseline (T_1_) (following consent and prior to randomisation and cluster allocation) and again at 18-22 weeks post randomisation (T_2_).

Each participating long-stay unit is assigned a RN who is responsible for blinded outcome assessment for all participating residents within that unit. All research nurses undertake a two-day preparation programme consisting of:

i) Training on the procedures and protocols surrounding the recruitment of participants and delivery, assessment and recording of all outcome measurements

ii) Simulated completion of all data collection instruments and forms

### Primary Outcome

The primary outcome is quality of life of residents as measured by the Quality of Life-AD (QOL-AD) instrument [26]. The QOL-AD covers 13 domains of quality of life. It is designed to provide both a care recipients (CR) report and a caregiver's (CG) report of the resident's QOL. The measure has good internal consistency, validity and reliability and has been recommended by the European consenus group on outcome measures for use in the measurement of psychosocial interventions in dementia [34].

The QOL-AD is administered as a structured interview using standardised instructions. The RN administers the QOL-AD form to the CR, regardless of the severity of dementia. A staff member who is familiar with the CR completes the caregiver proxy version of the QOL-AD. The RN is available to advise the designated staff member on how to complete the proxy version of the QOL-AD form, answering any questions that may arise in the process.

### Secondary Outcomes

(a) The level of agitation in resident participants is measured using the Cohen-Mansfield Agitation Inventory (CMAI). The CMAI is a 29-item scale specifically developed to assess the frequency of agitated and disruptive behaviours [35]. The questionnaire has four domains: physical/aggressive, physical/non-aggressive, verbal/aggressive, verbal/non-aggressive. The measure has good validity and reliability [36,37]. The CMAI is administered by the RN, following consultation with relevant staff who are aware of the resident's behaviour over the previous two weeks.

(b) Depression in resident participants is assessed using the Cornell Scale for Depression in Dementia (CSDD) [38]. The scale was specifically developed to assess signs and symptoms of major depression in people with dementia across five broad categories. As some people with dementia may not be able to provide reliable reports, the CSDD uses a comprehensive interviewing approach, through two semi-structured interviews: an interview with a main carer and an interview with the person with dementia. Good validity and reliability have been demonstrated for the scale [38].

(c) Staff care burden is assessed using a modified version of the Zarit Burden Interview [39]. The scale was initially developed to assess carer burden on the relatives of impaired older people. The original questionnaire contains 22 questions rated on a 4-point Likert scale and was designed to assess the impact of caring on the physical and emotional well-being of carers. The original scale has satisfactory reliability and validity [40]. A modified version of the original scale is used in this study, containing 13 questions selected for their appropriateness and applicability to nursing care staff in residential long-stay units. The modified scale has performed satisfactorily when used to assess burden on nursing staff caring for people with dementia in a Canadian long-stay setting [41].

